**ClinicalTrials.gov identification number: NCT04673422**

**Study duration and dates**

The study will start July 1st, 2020. Patient recruitment are proposed to last 25 months to start in January 2021 and end in January 2023. Data analyses, data cleaning, analysis and reporting will take a further 3 months.

## Introduction and Study Rationale

Dengue has been the growing public health problem in many tropical countries, including Thailand. (1) Almost 4 billion people were estimated to be at risk, with estimated 400 (95%CI: 284-528) million infections occurring annually. In Asia, around 10% of febrile patients were virologically confirmed with dengue. (2) In Thailand, Department of Disease Control reported the annual incidence between the year of 2015 and 2019 was 20 people per 100,000 population, with 10-20 annual mortality.

The most common cause of death is from dengue shock as a result of vascular leak syndrome. (3) This condition can occur in various clinical manifestations ranging from mild cases to life-threatening condition of dengue shock syndrome. The common sites of plasma leakage are pleural effusion and ascites (4) The contributing factors for endothelial dysfunction in dengue are cytokines such as soluble tumor necrosis factor receptor (sTNFR/75), interferon gamma, and vascular endothelial growth factor (4-7), NS1 antigenemia, complement activation, (8, 9) and activation of dendritic cells, macrophages, and mast cells (10)

Mast cells have recently been acknowledged as an important regulator for promoting innate immune responses. (11) Important composition of granules in mast cells are proteases, chymase and tryptase, histamine, heparin (12, 13) and leukotriene. (14) The activated mast cells can undergo degranulation, releasing these cytokines. These increase capillary permeability, leading to vascular leakage. (14, 15)

Leukotriene has an important role in promoting plasma leakage and leukocyte adhesion in postcapillary venules. (16) In dengue patients, leukotriene levels usually elevate during febrile and defervescence stage for 35 and 38 times of the baseline values, and return to baseline in convalescence stage. (17) Blocking leukotriene in dengue infected mice can significantly reduce plasma leakage (14).

The management of dengue consists of only symptomatic treatment, and intravenous fluid replacement. No specific treatment has yet been demonstrated of a benefit in preventing complications. (3) In the recent decades, mast cells have been demonstrated as a major contributor of severe forms of dengue, (10, 18) leading to research in reduction of vascular permeability with mast cell stabilizers or anti-histamine drugs. An animal model studies found that a tryptase inhibitor, nafamostat, (19) or leukotriene inhibitor, montelukast, could reduce the plasma leakage. (14)

In 2018, an open-label study found that patients with montelukast had a 22% absolute risk reduction in dengue shock syndrome, compared to standard treatment. (20) However, there has never been any randomized controlled trial evaluating the efficacy of montelukast in dengue patients.

## Study Design and Procedures

This randomized, prospective, 2-arm, parallel-group, double-blind, placebo-controlled superiority trial will evaluate the efficacy of montelukast in decreasing disease severity of dengue patients. The primary objective is to determine whether montelukast is more effective than placebo in reducing dengue with warning signs. Other important study objectives are to access the efficacy of montelukast in decreasing hemoconcentration, thrombocytopenia, hospitalization, length of hospital stay, severe dengue, dengue shock, and mortality.

The study cohort will include 358 patients aged 20 years or above with positive NS1 antigen test. Participants will be recruited over a 2-year period at 2 hospitals and will be followed up for up to 14 days.

The objectives are as follows:

### **Primary Hypothesis**

In dengue patients aged 20 years or above with positive NS1 antigen, does montelukast reduce the incidence of dengue warning signs? This hypothesis will be tested using a composite outcome including

- abdominal tenderness or pain
- persistent vomiting
- clinical fluid accumulation
- mucosal bleeding
- liver enlargement >2cm
- increase in hematocrit concurrent with decrease in platelet count

However, lethargy will be excluded as a criterion for warning sign as almost all patients reported subjective lethargy. (21)

### **Secondary Hypotheses**

The secondary hypotheses will address secondary outcome in analyses designed to support and confirm the primary analysis. These will include components of composite outcomes of dengue with warning signs, hospitalization, length of hospital stay, severe dengue, dengue shock, and mortality.

### **Eligibility Criteria**

The objective of setting inclusion/exclusion criteria is to identify a trial population that will ensure adequate event rates for statistical power and maximize safety. Inclusion/exclusion criteria were made as simple as possible to ensure standard implementation across all study sites. Specifically, the eligibility criteria were developed to identify patients with confirmed early dengue infection, hence, the trial population is comprised of individuals with NS1 antigenemia, which is usually found in a few days after symptom onset.

#### **Inclusion Criteria**

- at least 20 years old
- diagnosis of dengue
- positive NS1 or PCR test

#### **Exclusion Criteria**

- any warning sign of dengue
- concurrent diagnosis of other causes of fever, such as malaria or heat stroke
- pregnancy
- being unable to take medication by mouth
- critical illness needing intubation or admission to an intensive care unit
- being unable to communicate
- other indication of montelukast

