### **Baseline Information**

Once local regulatory requirements have been approved, investigator plans to identify potential study patients may be implemented. Participant informed consent must also be obtained prior to performing any procedures related to the trial. The following key elements are outlined in the study assessments and procedures below:

1. Verify participant's interest in study.
2. Obtain study consent
3. Continue collection of screening information, including such items as contact information, additional eligibility information, and medical history.
4. Confirmation that all inclusion/exclusion criteria satisfied
5. Completion of the study randomization procedure and baseline data collection

The following information will be recorded on the case record form by the attending clinicians:

- Patient details (e.g. date of birth, sex, weight)
- Dengue symptom onset date
- Major comorbidity (e.g. heart disease, diabetes, chronic lung disease)
- Date of hospitalisation
- Laboratory results
- Dengue serotypes
- Name of person completing the form

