#### **Withdrawal of consent**

A decision by a participant that they no longer wish to continue receiving study treatment should not be considered to be a withdrawal of consent for follow-up. However, participants are free to withdraw consent for some or all aspects of the study at any time if they wish to do so. In accordance with regulatory guidance, de-identified data that have already been collected and incorporated in the study database will continue to be used (and any identifiable data will be destroyed).

Patients should be withdrawn from study treatment if the following complications occur:

- Development of behavioural change, hallucinations, depression, suicidal thoughts and actions, sleepwalking, stuttering, tremor or shakiness, trouble sleeping, uncontrolled muscle movements
- Potential accidental administration of a dose of >10mg of montelukast a day (due to error in administration of study medication or accidental administration of non-study montelukast)

Figure 1 summarises the study design, Table 1 summarises the procedure.

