### Expected adverse events

Montelukast is well tolerated in in patients with asthma. (22) There were no significant differences between the montelukast and placebo treatment groups in the frequency of any adverse effect, with the exception of allergic rhinitis, which occurred more frequently in placebo than montelukast recipients.

In 2020, FDA required Boxed Warning about serious mental health side effects for montelukast, after 82 cases identified of completed suicide associated with montelukast, with many reporting the development of concomitant neuropsychiatric symptoms prior to the event. (23) Patients were suggested to stop taking montelukast and notify a health care professional if they experience behavior or mood-related changes while taking the medicine.

At each visit, the trial staff will specifically query participants for serious adverse events (SAEs). In addition, information on serious adverse events may also be reported to study staff spontaneously by participants through telephone calls. SAEs will be collected and reported from screening to the end of the study follow-up period for an individual participant. SAEs will be followed until resolution, stabilization, or until it is determined that study participation is not the cause. Reports of serious adverse events will be collected for review by the DSMB at their meetings.

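### A cheap safety improvement, not an error: patients with active suicidal thoughts, hallucinations or a current depressive episode can start study drug, and the stopping rule names new symptoms but not worsening

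*Protocol*

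**What the plan says.** Protocol, Exclusion Criteria, lists seven reasons for exclusion: existing warning signs, another cause of fever, pregnancy, inability to swallow medicines, critical illness, inability to communicate, and "other indication of montelukast". None concerns mental state, and the Inclusion Criteria add nothing on it.

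Protocol, Eligibility Criteria, gives the purpose of the criteria: to "identify a trial population that will ensure adequate event rates for statistical power and maximize safety". It also says "Inclusion/exclusion criteria were made as simple as possible to ensure standard implementation across all study sites".

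Protocol, Expected adverse events, records the regulatory background: "In 2020, FDA required Boxed Warning about serious mental health side effects for montelukast", following "82 cases identified of completed suicide associated with montelukast". It then reports the accompanying advice: "Patients were suggested to stop taking montelukast and notify a health care professional if they experience behavior or mood-related changes while taking the medicine".

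Protocol, Withdrawal of consent, sets the trial's own rule for stopping study treatment. Its first trigger is "Development of behavioural change, hallucinations, depression, suicidal thoughts and actions, sleepwalking, stuttering, tremor or shakiness, trouble sleeping, uncontrolled muscle movements".

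Protocol, Baseline Information, step 3, reads "Continue collection of screening information, including such items as contact information, additional eligibility information, and medical history". Step 4 then confirms the listed criteria, and step 5 randomizes. The comorbidities given as examples are cardiac, diabetic and pulmonary; psychiatric history is not named.

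**The concern.** The Protocol recognises a serious psychiatric risk of the study drug and acts on it only after dosing has begun. Two gaps follow.

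The first is at entry. A patient who can communicate and who has suicidal thoughts on day 1 meets every written criterion. History is taken before randomization, and a careful clinician may well decline to enrol such a patient, but no criterion tells staff to do so.

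The second is on treatment. If a depression present at entry deepens, it is not clear that anything has developed. One clinician could stop drug under behavioural change while another continues because no new symptom has appeared.

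What is at stake is participant safety and a stopping rule applied alike at the two hospitals. Treatment is double-blind and randomized, so neither arm is favoured.

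**Working it through.** There is no figure in the plan to reproduce on this point. The check is a reading of the sections against each other, followed by an illustration of scale.

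**Reading the rules against four cases**

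| Case | Entry criteria | Stopping rule | Reported regulatory advice |
|---|---|---|---|
| A. Well at entry, suicidal thoughts on day 2 | Eligible | Stops drug | Stop |
| B. Suicidal thoughts already present on day 1, unchanged | Eligible | Not clearly triggered | No change on drug, so silent |
| C. Depression at entry, mood deepens, behaviour unaltered | Eligible | Not clearly triggered | Stop (a change in mood) |
| D. Depression at entry, new suicidal thoughts | Eligible | Stops drug | Stop |

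Case B is the entry gap: a symptom that ends treatment if it appears on day 2 is no bar to starting on day 1. Case C is the wording gap: the trial's rule is narrower than the advice the Protocol reports. Cases A and D show that the existing rule already works for symptoms that are new, including new symptoms in a patient with earlier depression.

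**Does anything else close the gaps?** Step 4 of Baseline Information checks only the listed criteria. Table 1 schedules a general examination and clinical evaluation on day 1 and side-effect monitoring throughout, without content specific to mental state. Specific questioning at visits is for serious adverse events, and the monitoring board reviews those afterwards. None of these sets an entry rule or records a pre-dose state against which a change could be judged. The first dose is to be given at once, so the questions have to come before randomization.

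**Scale**

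Inputs: 358 patients (Study Design and Procedures), 1:1 allocation (Randomization and allocation concealment), 25 months of recruitment (Study duration and dates), 10 mg daily for at most 10 days (Administration of allocated treatment). The proportion *p* of otherwise eligible patients with one of the three conditions is **not in the documents**; 1%, 3% and 5% are assumed.

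- Planned pace: 358 / 25 = 14.32 patients per month.
- Maximum exposure: 10 × 10 mg = 100 mg per patient.

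| Quantity | Formula | *p* = 1% | *p* = 3% | *p* = 5% |
|---|---|---|---|---|
| Affected patients randomized now | 358*p* | 3.6 | 10.7 | 17.9 |
| Of these, on montelukast | 358*p* / 2 | 1.8 | 5.4 | 9.0 |
| Extra patients to find if excluded | 358/(1 − *p*) − 358 | 3.6 | 11.1 | 18.8 |
| Extra recruitment, months | 25*p*/(1 − *p*) | 0.25 | 0.77 | 1.32 |

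These are counts of patients exposed. The Protocol gives no event risk over 10 days and no denominator for the 82 cases, so no number of patients harmed can be derived.

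**The case against.** The best reply is that nothing here is wrong. The reported warning concerns effects that emerge on drug, its remedy is to stop, and the stopping rule carries that out. Its opening trigger, behavioural change, requires no new diagnosis. New suicidal thoughts or hallucinations stop drug whatever the history. Exposure is at most 10 doses, outpatients are seen no less often than on alternate days, and participants may stop treatment while remaining in follow-up. The sponsor also chose simple criteria deliberately.

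Most of this stands. It reduces the wording gap to case C, a decline in mood without altered behaviour or another listed symptom, and makes that the weaker half of the point. It leaves the entry gap open, because no written rule addresses case B. One short line is compatible with simple criteria, and a written rule serves uniform practice at two sites better than unwritten discretion.

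A second objection also stands: a worsening clause covering every listed symptom would be too broad. Poor sleep and shakiness may come from the fever itself, and patients enter early in the illness, so such a clause could force stops for ordinary dengue. Depression without qualification would likewise be read differently at each site. The proposed change is limited accordingly.

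Four stronger readings are tempting and unsupported:

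- *The entry and stopping rules contradict each other.* They do different jobs; one governs who enters and the other what happens on drug.
- *Existing depression is a contraindication, or raises the risk from montelukast.* The Protocol says neither.
- *The exposure counts measure harm.* They rest on an assumed prevalence and no event risk.
- *The efficacy comparison is biased.* Randomization and blinding spread such patients over both arms, and the primary analysis is by intention to treat.

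**Conclusion.** The point holds as a recommended safety improvement, not as the correction of an error. Two facts are plain from the text: no exclusion covers active suicidality, hallucinations or a current depressive episode, and the stopping rule does not name worsening although the advice reported in the same Protocol covers any change in behaviour or mood. The case for acting is that the possible harm is grave, the change is small, and the criteria are said to aim at safety.

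The size is unknown. On the assumed 1% to 5%, roughly 2 to 9 affected patients would be given montelukast, each for at most 10 days. The recommendation rests on prudence and on clarity of the rule, not on those counts. Both rules are protocol content, so a separate statistical analysis plan would not be expected to supply them.

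**What to change.** 1. **Exclusion Criteria.** Add one line: *active suicidal thoughts or actions, hallucinations, or a current depressive episode by clinician assessment*. Past or stable treated depression does not by itself exclude.
2. **Withdrawal of consent.** Add *or worsening from baseline* for four items only: behavioural change, depression, suicidal thoughts or actions, and hallucinations. Leave sleep, tremor and the remaining items triggered by development alone. With the new exclusion in place, this clause mainly serves patients who enter with lesser or treated mood symptoms.
3. **Baseline Information, step 3.** Ask about these four items within the history already taken, before step 4 and the first dose, so that later change has a comparator.

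The cost is one criterion, a few words and a few questions, with no extra visit. A small number of patients, not documented, become ineligible; under the assumed range this is about 4 to 19 more patients to find, or 0.3 to 1.3 months. A few more patients may stop drug. They stay in the intention-to-treat analysis, where stops on montelukast could dilute the effect slightly. Sample size, allocation and the method of analysis do not change.

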## **Recruitment: Informed Consent, Screening, Baseline**

### **Recruitment**

The goal of participant recruitment is to create a trial population that will ensure adequate event rates for statistical power while maximizing participant safety to the population for which the intervention is intended. Recruitment strategies may also include dissemination of information about this trial to laboratory professionals who test NS1 antigen from the patient specimens.

### **Regulatory and Ethical Considerations, including the Informed Consent Process**

The study will be conducted in accordance with Good Clinical Practice (GCP), all applicable subject privacy requirements, and the guiding principles of Helsinki, including Institute Review Board (IRB) of both the Royal Thai Army Medical Department and related hospitals review and approval of study protocol and any subsequent amendments.

### **Existing Populations in the Clinical Site Practices**

Methods for identifying potentially eligible participants within the clinical practice of the research settings is a targeted alert of positive laboratory results by attending physicians.

### **Baseline Information**

Once local regulatory requirements have been approved, investigator plans to identify potential study patients may be implemented. Participant informed consent must also be obtained prior to performing any procedures related to the trial. The following key elements are outlined in the study assessments and procedures below:

1. Verify participant's interest in study.
2. Obtain study consent
3. Continue collection of screening information, including such items as contact information, additional eligibility information, and medical history.
4. Confirmation that all inclusion/exclusion criteria satisfied
5. Completion of the study randomization procedure and baseline data collection

The following information will be recorded on the case record form by the attending clinicians:

- Patient details (e.g. date of birth, sex, weight)
- Dengue symptom onset date
- Major comorbidity (e.g. heart disease, diabetes, chronic lung disease)
- Date of hospitalisation
- Laboratory results
- Dengue serotypes
- Name of person completing the form

### **Randomization and allocation concealment**

Eligible patients will be randomized using a computer-generated randomisation list prepared by an independent statistician and stratified by the centre with a block size of four in a 1:1 ratio to one of the two treatment arms:

Arm 1: montelukast 10 mg

Arm 2: placebo 10 mg

### **Administration of allocated treatment**

Study medication will be given 10 mg orally immediately and every day thereafter for 10 days or until recovery, defined as the discontinuation of the follow up appointment by the attending physicians, whichever is shorter.

### **Collecting follow-up information**

The following information will be ascertained at least every other day for 14 days or until the discontinuation of the follow up appointment by the attending physicians, whichever is shorter.

- Clinical symptoms and signs of warning signs

- Hospitalisation status, death status
- Laboratory results

Follow-up information is to be collected on all study participants, irrespective of whether or not they complete the scheduled course of allocated study treatment. Study staff will seek follow-up information through various means including medical staff, reviewing information from medical notes, routine healthcare systems, and registries.

#### **Duration of follow-up**

All randomised participants are to be followed up until the discontinuation of the follow up appointment by the attending physicians, whichever is shorter. It is recognised that in the setting of this trial, there may be some variability in exactly how many days post-randomisation information on disease status is collected. This is acceptable and will be taken account of in the analyses and interpretation of results, the principle being that some information about post-randomisation disease status is better than none.

#### **Withdrawal of consent**

A decision by a participant that they no longer wish to continue receiving study treatment should not be considered to be a withdrawal of consent for follow-up. However, participants are free to withdraw consent for some or all aspects of the study at any time if they wish to do so. In accordance with regulatory guidance, de-identified data that have already been collected and incorporated in the study database will continue to be used (and any identifiable data will be destroyed).

Patients should be withdrawn from study treatment if the following complications occur:

- Development of behavioural change, hallucinations, depression, suicidal thoughts and actions, sleepwalking, stuttering, tremor or shakiness, trouble sleeping, uncontrolled muscle movements
- Potential accidental administration of a dose of >10mg of montelukast a day (due to error in administration of study medication or accidental administration of non-study montelukast)

Figure 1 summarises the study design, Table 1 summarises the procedure.

**Figure 1: study design**

[figure not shown]

